### Ethical Considerations

The trial has been granted ethics approval by the research ethics committee (East Midlands-Nottingham 1), the Health Research Authority, and the Health and Care Research Wales Committee (reference number 23/EM/0109) and has received favorable approvals from the research and development governance bodies of the participating NHS trust sites. The study has also been reviewed by the National Institute of Health and Care Research Applied Research Collaboration East Midlands (ARC-EM) Scientific Committee as part of the funding application.

The trial will be overseen by an independent ARC-EM Scientific Committee. The members of the committee will be drawn from outside the institutions where the research team currently works to ensure the committee’s independence from the research team. It will serve the function of a trial steering committee and a data monitoring committee. The trial will be reviewed every 6 months through reports to the ARC-EM Scientific Committee and presentations of progress to the committee by the study team. The data monitoring committee will review safety data and periodically review the conduct of the study. The steering committee will take responsibility for the scientific validity of the study protocol, assessment of study quality and conduct, and the scientific quality of the final study report. The sponsor and the investigators participating in the trial bear the final responsibility for the conduct of the trial. The trial will be conducted in accordance with the ethical principles that have their origin in the Declaration of Helsinki, the principles of Good Clinical Practice, and the UK Department of Health Policy Framework for Health and Social Care.

All participants will sign the participant consent form. Participants will be informed in the PIS that entry into the trial is entirely voluntary and that their health care, work, and legal rights will not be affected by their decision. Furthermore, it will be explained that they can withdraw at any time during the trial (including at follow-up) but that in the event of their withdrawal, data collected up to that point cannot be erased and may still be used in the final analysis. It will also be clearly stated in the PIS that potential participants who decide not to take part in the trial can proceed with enrolling in the respective or other well-being interventions delivered routinely at a given site (but are not part of the trial). Moreover, for intention-to-treat (ITT) purposes, as stated in the PIS, participants will have the right to decide not to withdraw from the trial entirely but withdraw from the program (intervention) while they may still contribute to the trial by completing the web-based survey at the 3 follow-up time points, or they can carry on with their participation in the program but withdraw their partaking in the completion of the web-based survey at the follow-up time points. Insurance and indemnity for trial participants and trial staff are covered within the NHS Indemnity Arrangements for clinical negligence claims in the NHS, issued under the cover of Health Systems Global 96/48. There are no special compensation arrangements, but trial participants may have recourse through the NHS complaint procedures. The University of Nottingham, as the research sponsor, indemnifies its staff with both public liability insurance and clinical trials insurance for claims made by research participants.

### Randomization and Blinding

Once consent is obtained on the REDCap platform, they will be randomly allocated in a 1:1 ratio to either the MBCT-L or SRP intervention. The online format and delivery of the interventions allow the allocation of participants to take place across the participating sites; this is expected to facilitate timely and sufficient recruitment within and across the intervention groups running at any site until the 2 intervention groups are full in each recruitment wave throughout the trial. Randomization will be conducted via a web-based randomization system set up by a clinical decision support system supported by the University of Nottingham. The randomization system will ensure that all the researchers involved in the outcome assessments ([name]) remain blinded to intervention allocation. Participant allocation to either intervention arm will be solely facilitated by a project administrator who will manage the randomization system independently of the research team following specified standard operating procedures. The study statistician will also be blinded to treatment allocation. In the event of inadvertent unblinding, the details of the unblinding incident will be recorded in the study log, relevant sponsor and monitoring committees will be informed (eg, the university sponsor, the research ethics committee, and the ARC-EM Scientific Committee), and the extent and impact of the unblinding will be assessed. All participants will complete the same outcome measures in the survey, so that researchers or outcome assessors will not be able to determine the participant’s group based on the response. In view of the nature of the interventions, participants cannot be blinded; they will be informed of which treatment arm they have been randomized to and will be notified through a letter or via email sent to them by the project administrator, which will also include information on the intervention delivery (eg, dates and times, requirements for attendance, and joining instructions).

### Interventions

#### Overview

The 2 interventions that participants will be randomized, MBCT-L or SRP, will be delivered online via a videoconferencing platform, that is, Microsoft Teams, taking place in a group format once a week at different times and days, allowing participants to indicate (at the time of consent) which group times they would opt for if they were to be randomized to either intervention. The sessions on either intervention will not be recorded. There will be 3 recruitment waves in total, with the interventions starting at various time points during a given recruitment wave and both intervention arms starting in the same week in each recruitment wave to allow synchronized data collection. The CONSORT (Consolidated Standards of Reporting Trials) flowchart (Figure 1) depicts an outline of recruitment, consent, randomization, and assessment processes.

**Figure 1 figure1:**
[figure not shown]
CONSORT (Consolidated Standards of Reporting Trials) flowchart—revised. CF: consent form; MBCT-L: Mindfulness-Based Cognitive Therapy for Life; NHFT: Nottinghamshire Healthcare National Health Service Foundation Trust; NUH: Nottingham University Hospitals; PIS: participant information sheet; SPFT: Sussex Partnership National Health Service Foundation Trust; SRP: Stress Reduction Psychoeducation; TEWV: Tees, Esk and Wear Valleys National Health Service Foundation Trust.

#### The MBCT-L Intervention

MBCT-L integrates conventional cognitive therapy techniques with stress reduction techniques and mindfulness practice, as in the original MBCT version, but has been adapted to apply to the general population as per established protocol [9]. The program includes 8 online weekly sessions lasting approximately 2 hours and an online practice day lasting approximately 6 hours. MBCT-L will run for 9 consecutive weeks or 10 weeks if a 1-week break is included (eg, due to school break or holidays) in a group-based format with an average of 8 participants recruited per group. The content includes themed teaching every week and guided meditation practices (eg, breathing practice and body scan), as well as everyday homework practices lasting 30 to 45 minutes. Participants will receive frequent automated text reminders about their upcoming sessions and homework or home practices via an automated text messaging service provided by a Generated Health system, Florence [27]. The program will be delivered by approximately 8 trained MBCT practitioners or facilitators across the main NHS trust sites, who are part of the teaching team involved in the MBCT-L interventions already being offered to public sector staff through the NHS trust services and have been trained under, and follow, the same MBCT training protocol [9].

The MBCT-L program broadly follows an overarching structure of developing mindfulness skills intended to enhance attentional control and awareness, cultivating a deeper understanding of how distress is created and maintained and how mindfulness training can address factors that contribute to its maintenance, learning skillful ways of relating to experience developed through awareness and practice, and learning to recognize unhelpful reactive patterns in everyday life and cultivate the capacity to respond to these with mindfulness and compassion. In the second part of the program, participants practice the application of this learning to everyday life, including work, to respond more effectively to stress and enjoy the positive aspects of life.

#### The SRP Intervention

The SRP intervention will be delivered in 4 online weekly sessions lasting approximately 2 hours and running for 4 consecutive weeks or 5 weeks if there is a 1-week break (eg, school break or other holidays). The program will run as it is currently being offered as standard care across Nottinghamshire and all the other regions in England, through NHS Talking Therapies (formerly known as Improving Access to Psychological Therapies) or NHS trust or other health care services. Its content is focused on psychoeducation around well-being and stress management, combined with relaxation strategies [23]. Specifically, the program consists of sessions focused on areas of stress, well-being, and goal setting; sleep hygiene; anxiety and depression; behavioral activation; problem-solving; thinking errors; and a final recap, review of goals and thoughts for future well-being. Participants will be encouraged to work between sessions by engaging in a stress reduction technique of their preference daily for approximately 30 minutes and through a diary activity (eg, behavioral activation diary). They will receive email reminders to complete these and attend the upcoming sessions.

Recognizing that SRP programs can vary in their content and format or structure in how they are being offered across NHS trusts and other organizations in the United Kingdom, the standard 4-session structure will be adopted as the optimized form of its delivery. The SRP will also explicitly avoid embedding any mindfulness-based techniques, as these are not core or essential elements of a stress reduction approach, while it is important for the RCT to adhere to NICE-recommended standards, which indicate that 4 sessions are optimal when group sessions are delivered by experienced facilitators. The program will be delivered by 3 experienced facilitators (2 psychological well-being practitioners and 1 psychiatrist) across the SRP groups recruited across all sites, ensuring consistent delivery of the intervention across all participating NHS sites.

#### Intervention Compliance

Intervention adherence, compliance rates (ie, session attendance), and any other data specific to the intervention, where applicable, will be collected electronically via a password-protected Microsoft Online Form, as per routine therapy protocol during the MBCT-L and SRP interventions. Retention rates and turnover by randomized group will be determined after the first recruitment wave. We will consider participants as compliant if they have attended 50% of the sessions on either intervention. Participants will not be allowed to continue with the intervention if they miss the first couple of sessions in either intervention arm. Participant attendance will be recorded by the facilitators for each intervention, as per routine practice, and reported to the project administrator, who will monitor attendance and contact participants if they miss the first or second session. Home practice adherence will not be monitored or recorded; as per routine practice, participants will be strongly encouraged to engage in home practice outside the formal weekly sessions; however, a potential lack of daily commitment to practice should not affect participants’ session attendance. Practitioners or facilitators will prompt participants to complete their daily home practice between intervention sessions and remind them of the upcoming intervention sessions.

### Outcome Assessments

#### Overview

Participants who provide consent will be required to complete the outcome assessments via web-based surveys through REDCap, which will contain the primary and secondary measures at baseline (before the intervention); up to 2 weeks before randomization; and at follow-up time points at weeks 6, 12, and 20 after randomization. Participants in both arms will receive the same outcome measures. Participants will be able to save their responses and return to the survey to complete their assessments at a later point. For both incomplete baseline and follow-up surveys, participants will receive 3 automated email reminders through REDCap asking them to complete the survey. If the survey is still incomplete, the research team may then send out 1 further personalized email reminder from the study email address.

#### Primary Outcome

The primary outcome will be the change in the PSS-14 [24] score from baseline to 20 weeks after randomization. The PSS-14 was selected as the primary outcome measure as it is a well-validated and internationally used self-report scale of perceived stress and has been widely used in previous trials assessing changes in stress levels in diverse populations, including public sector workers.

#### Secondary Outcomes

All secondary outcome measures used in the trial are widely recognized as valid and effective scales in assessing well-being, mental health state, and work-related engagement and performance in various populations, including health care workers. Although these measures are relatively brief to administer, they present limitations due to their reliance on self-report, which can entail biases, such as recall bias, and may not index the full complexity of an individual’s experience of stress or poor well-being. Secondary outcomes will all be collected at 6, 12, and 20 weeks after randomization. These standardized measures have been commonly used in intervention studies to assess changes in well-being, mental health state, work-related satisfaction, engagement, and performance (Textbox 2 [24,28-33]).

Secondary measures used in the trial.Perceived Stress Scale-14 [24]: This is a self-report scale that assesses the degree to which the respondent has perceived situations in their life as stressful within the past month. Responses are obtained through 14 items requiring ratings of statements from 0 (never) to 4 (very often). The assessment at 6 and 12 weeks will be treated as secondary outcomes.Generalized Anxiety Disorder-7 [28]: This is a 7-item instrument used to measure or assess the severity of generalized anxiety disorder. Each item asks the individual to rate the severity of their symptoms over the past 2 weeks. Response options range from 0 (not at all) to 3 (nearly every day).Patient Health Questionnaire-9 [29]: This is a 9-item scale used to measure the severity of depression. Each item asks the individual to rate how often they have been bothered by the listed symptoms over the past 2 weeks, with responses ranging from 0 (not at all) to 3 (nearly every day).The International Trauma Questionnaire [30]: This is a brief measure of posttraumatic stress disorder and complex posttraumatic stress disorder. Respondents are asked to think of an experience that troubles them the most and indicate how much they have been bothered by that experience in the past month by responding to 18 questions on a scale from 0 (not at all) to 4 (extremely). Questions refer to ways people typically feel, think about themselves, and relate to others.Five Facet Mindfulness Questionnaire [31]: The questionnaire items assess 5 aspects of mindfulness and their impact on well-being. Participants are required to rate statements on a 5-point scale from 1 (never or very rarely true) to 5 (very often or always true) on facets of mindfulness relating to describing, observing, nonreacting, acting with awareness, and nonjudging.Copenhagen Burnout Inventory [32]: This measures personal and occupational burnout in 19 items, including overall physical and psychological fatigue (6 items), physical and psychological fatigue related to work (7 items), and client-related burnout (6 items). Answers include “always, often, sometimes, rarely, and never or almost never” or “to a very high degree, to a high degree, somewhat, to a low degree, and to a very low degree.” The possible score range for the burnout scales is 0 to 100 (response options are coded in scores of 100, 75, 50, 25, and 0). Higher scores indicate a higher degree of exhaustion.Utrecht Work Engagement Scale-9 Item [33]: This measures 3 dimensions of work engagement, including vigor (3 items), dedication (3 items), and absorption (3 items). Items are presented as statements to which persons respond on a 7-point scale, with anchors 0 (never) and 6 (always or every day).

#### Economic Evaluation

We also plan to conduct an economic evaluation from the perspective of the NHS and personal social services.

#### Measures of Cost-Effectiveness

The primary measure of cost-effectiveness includes the incremental cost-effectiveness ratio (ICER) per quality-adjusted life year (QALY) gained for the MBCT-L versus SRP interventions.

Secondary measures include ICER per reduction in PSS-14 scores for MBCT-L versus SRP.

The following outcome data will be collected:

Health-related quality of life outcomes will be collected at baseline and 6, 12, and 20 weeks after randomization. These will be measured via the widely used EQ-5D-5L [34].A health economics assessment adapted from the Client Service Receipt Inventory [35], which has been successfully used in a wide variety of studies of mental health, community-based health, and social care services, will be conducted. A mental health customized version will be administered to collect self-reported resource use for 6 months preceding data collection at baseline, 6 weeks preceding data collection at 6-week follow-up, 6 weeks preceding data collection at 12-week follow-up, and 8 weeks preceding data collection at 20-week follow-up. It is intended that the data gathered from these measures will be used for a cost-effectiveness analysis, subject to trial outcomes, should MBCT be superior to SRP.

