While a broad range of organizational- and individual-level well-being interventions are currently being offered in National Health Service (NHS) trusts and other public sector workplaces, Stress Reduction Psychoeducation (SRP) is a standard usual care group program offered widely and in various formats across all geographic regions in England (United Kingdom) to health care staff as well as other public sector staff accessing psychotherapeutic interventions through their organizational well-being services affiliated with NHS trusts. Mindfulness-Based Cognitive Therapy for Life (MBCT-L) [9] is a newer, third-wave intervention, which is increasingly being implemented in the NHS and other public sector services. MBCT-L borrows its premises from the standard Mindfulness-Based Cognitive Therapy (MBCT) variant [10,11], which is a NICE-recommended treatment option for recurrent and mild to moderate acute depression [12], and is also included in clinical guidelines as a relapse prevention option in other countries [13-15]. Importantly, MBCT-L is an adaptation tailored to nonclinical populations and has been shown to be effective in improving well-being and mental health outcomes in various populations, including health care workers, as evidenced in previous work [16-20], including a recent randomized controlled trial (RCT) that showed moderate to large effects on health care staff well-being derived from MBCT-L compared to a waitlist control [21].

SRP and MBCT-L approaches are increasingly being implemented across the NHS trusts in the United Kingdom in online formats, particularly after the COVID-19 pandemic, in acknowledgment that digital modalities can overcome main barriers to intervention uptake and adherence [22]. However, MBCT-L is currently being offered as a workplace psychological program through the NHS trust’s well-being services in a limited number of trusts across the United Kingdom. Notably, MBCT-L is a longer-duration program, commonly lasting 8 or 9 weeks if a practice (retreat) day is included, as opposed to SRP, the duration of which can vary between 4 and 6 weeks. Furthermore, MBCT-L requires more skilled staff for its delivery, that is, specifically MBCT-trained staff, whereas SRP programs can be delivered by classically trained cognitive behavioral therapy practitioners, psychological well-being practitioners, or other health care staff trained in supporting people with common mental health problems in managing their conditions.

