### Study Rationale

The NICE review did not include any online mindfulness-based studies, while the included stress management interventions were delivered either face-to-face or online. All 5 mindfulness-based studies and all 5 stress management studies included in the NICE review had a waitlist or usual care as a comparator or no well-being comparator intervention. Only 1 of the stress management studies was based in the United Kingdom, while there were no other mindfulness-based studies that were conducted in the United Kingdom. Finally, while the NICE review consolidated some qualitative data assessing barriers and facilitators to intervention uptake, it only included 1 qualitative study, which involved another type of intervention, that is, digital cognitive behavioral therapy [8]. The findings of the study indicated that there are a number of positive aspects of the digital modality of such a well-being intervention, including convenience and discreteness or anonymity, while specific barriers (eg, time pressures) and drivers (eg, managerial support) were reported to impact engagement with the given intervention.

Therefore, in light of the lack of online mindfulness-based studies in the NICE review and a lack of studies directly comparing mindfulness-based and SRP approaches, the proposed superiority trial will assess the effectiveness and cost-effectiveness of the 2 approaches. Furthermore, in light of the lack of qualitative studies exploring the acceptability or effectiveness of either approach, this study aims to gather in-depth qualitative data from a subsample of participants to explore the perceived impact of the intervention, including postintervention changes in well-being and work performance, barriers and facilitators to the uptake and acceptability of such interventions, and their engagement throughout the program. The overarching research question is as follows: Does MBCT-L demonstrate superior efficacy to SRP in reducing perceived stress and improving mental health and work-related outcomes among public sector employees? The findings of this study are expected to fill in the aforementioned gaps in the existing research and are intended to inform the NHS and other public sector organizations on how to best invest in their future resource provision to retain and support their staff at risk of poor well-being.

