## Methods

### Aim, Design, and Setting of the Study

#### Overview

The proposed Well at Work study is a single-blind, multisite, parallel-group, 2-arm superiority RCT that aims to assess the clinical effectiveness and cost-effectiveness of MBCT-L versus SRP in health care and other public sector staff who are seeking to access well-being support through human resource channels affiliated with the participating NHS trusts. The primary objective of this trial will be to determine whether there is a difference in change in the primary outcome on the Perceived Stress Scale-14 (PSS-14 [24]) between the 2 intervention groups from baseline to 20 weeks after randomization. The secondary objectives will be to assess the differences in change in any of the secondary mental well-being and work-related outcome measures between the 2 arms from baseline to each follow-up time point, that is, at 6, 12, and 20 weeks after randomization. Recruitment, interventions, and assessments will be conducted remotely via online platforms using videoconferencing and electronic technologies.

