#### Economic Analysis

The initial estimates of cost-effectiveness will require a base case analysis before exploring the impact of uncertainty. To perform the base case analysis, first, each individual participant within the trial will have an estimated intervention cost, a health care cost, a QALY score based upon their EQ-5D-5L responses, and a PSS-14 score. Second, using ordinary least squares regression, incremental costs, QALYs, and PSS-14 scores will be estimated for MBCT-L versus SRP groups. These incremental values will then be used to estimate the ICER per QALY gained and the ICER per PSS-14 reduced. The base case analysis will use data from all participants who report complete data; however, a secondary analysis using all participants’ data will be conducted, with missing data controlled for using multiple imputation [37].

The base case analysis will not include any productivity costs (ie, due to absence from work), as per NICE guidelines [39]. A secondary analysis will be conducted, whereby productivity costs will also be included, using a similar approach as the base case analysis. All analyses will be conducted using the latest version of Stata. Multimedia Appendix 3 provides a detailed economic analysis plan.

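### One sentence makes the cost-effectiveness analysis depend on MBCT-L being superior, contradicting the unconditional cost-effectiveness aim and plan stated elsewhere in the protocol

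*Protocol article*

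**What the plan says.** The condition appears once, at the end of the section Measures of Cost-Effectiveness. It covers the EQ-5D-5L and the adapted Client Service Receipt Inventory, and says these data "will be used for a cost-effectiveness analysis, subject to trial outcomes, should MBCT be superior to SRP".

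Elsewhere the protocol article attaches no such condition:

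- Study Rationale: "the proposed superiority trial will assess the effectiveness and cost-effectiveness of the 2 approaches".
- Aim, Design, and Setting, Overview: the study "aims to assess the clinical effectiveness and cost-effectiveness of MBCT-L versus SRP in health care and other public sector staff".
- Economic Evaluation: "We also plan to conduct an economic evaluation from the perspective of the NHS and personal social services".
- Economic Analysis: "The initial estimates of cost-effectiveness will require a base case analysis before exploring the impact of uncertainty". The section then sets out the complete-case base case, a multiple-imputation analysis and an analysis that adds productivity costs.
- Discussion, Anticipated Findings: only the budget impact analysis is made to depend on the clinical and cost-effectiveness results. That presupposes that a cost-effectiveness result exists.

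On the measures themselves: "The primary measure of cost-effectiveness includes the incremental cost-effectiveness ratio (ICER) per quality-adjusted life year (QALY) gained" and "Secondary measures include ICER per reduction in PSS-14 scores for MBCT-L versus SRP".

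**The concern.** The same analysis is an aim of the trial in some sections and contingent on a favourable clinical result in another. A reader cannot tell which governs, and the choice could be made after the primary result is seen.

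The condition is also a poor fit. Superiority is judged on PSS-14, while the primary economic measure is built from EQ-5D-5L QALYs and costs. A PSS-14 difference that misses significance says nothing definite about incremental costs or QALYs. The Background states that "MBCT-L is a longer-duration program, commonly lasting 8 or 9 weeks if a practice (retreat) day is included", against 4 to 6 weeks for SRP, and that it calls for specifically trained staff. If MBCT-L is not shown to be better, the cost difference is what a commissioning service needs. The Study Rationale says the findings should guide how public sector organisations invest in staff support. Under the conditional sentence, a null or inconclusive trial would give them no cost evidence.

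**Working it through.** **1. What the condition covers.** The gated data are the EQ-5D-5L and service-use data, the inputs to QALYs and health care costs. The condition therefore reaches the primary economic measure as well as cost per PSS-14 point.

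**2. Why cost matters.** From the Interventions section, MBCT-L has 8 sessions of about 2 hours plus a practice day of about 6 hours: 8 × 2 + 6 = 22 contact hours. SRP has 4 sessions of about 2 hours: 4 × 2 = 8 contact hours.

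**3. Reproducing the plan's sample size.** Inputs from Sample Size: difference 5, SD 7.7, two-sided alpha 0.05, baseline to follow-up correlation 0.2, correlation among follow-ups 0.7, ICC 0.15.

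- Variance factor for the mean of three follow-ups with baseline adjustment: (1 + 2 × 0.7)/3 − 0.2² = 0.80 − 0.04 = 0.76.
- Per arm at 90% power: 2 × (1.960 + 1.282)² × 7.7² × 0.76 / 5² = 37.9, so 38, total 76. This matches.
- Inflation: 76 × (1 + 7 × 0.15) / 0.75 = 76 × 2.05 / 0.75 = 207.7, so 208. This matches.
- Revision at 85% power: 32.4 per arm, so 33, total 66. Then 66 × (1 + 9 × 0.15) / 0.62 = 66 × 2.35 / 0.62 = 250.2. 26 groups of 10 give 260, which is consistent.

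**4. Standard error of the 20-week difference.** Analysed number: 260 × 0.62 = 161.2. Variance factor for one follow-up: 1 − 0.2² = 0.96. SE = √(4 × 7.7² × 0.96 × DE / 161.2) = √(1.412 × DE).

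- 10 per group: DE = 2.35, SE = 1.82.
- About 6.2 analysed per group (10 × 0.62): DE = 1 + 5.2 × 0.15 = 1.78, SE = 1.59.

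**5. How often the analysis would not be run.** Assumption: superior means an estimate favouring MBCT-L by more than 1.96 SE. P(not run) = Φ(1.96 − d/SE), where d is the true difference. The mean estimate when the analysis is run is d + SE × φ(a)/(1 − Φ(a)), with a = 1.96 − d/SE. A simulation agreed with these values.

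| True difference | Not run (SE 1.59 / 1.82) | Mean PSS-14 benefit when run |
|---|---|---|
| 5 | 12% / 22% | 5.35 / 5.68 (7% / 14% too large) |
| 3 | 53% / 62% | 4.33 / 4.84 (44% / 61% too large) |
| 0 | 97.5% / 97.5% | not expressed as a ratio |

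The 3-point row is illustrative; the protocol gives no such scenario.

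**6. Sensitivity.** If the test used the average of the three follow-ups, as the sizing formula does, the SE would be 1.62 (10 per group) or 1.41 (6.2 per group). At a true 5 points the analysis would then not be run in 13% or 6% of trials.

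**The case against.** The strongest reply is that one hedged sentence, framed as an intention, should not be taken as the settled plan. Economic Evaluation and Economic Analysis are unconditional, and the detailed economic plan in Multimedia Appendix 3, which is not at hand, may settle the matter. This stands in part. A reader might infer that the sponsor has firmly decided to drop the economics after a non-superior result. The document does not support that; it contradicts itself. But the condition is in print, so condensation into an article does not explain it, and the sentence would need correcting even if the appendix resolves the question.

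Second, the protocol does not define superior for this purpose. That is right, and every percentage above depends on the reading stated in step 5. The contradiction and the misfit with a cost-per-QALY measure do not.

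Third, a reader might infer that the cost-effectiveness result itself is biased upward. The documents do not support that. The condition leaves the estimate in any given trial unchanged; it selects which trials receive an economic analysis. At the planned effect the resulting overstatement of the PSS-14 benefit is modest. For QALYs it depends on a correlation with PSS-14 that the documents do not give, and is nil if that correlation is zero. With a positive incremental cost, an overstated benefit makes the cost per PSS-14 point too low, that is, too favourable.

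Finally, cost-effectiveness is in the aim and rationale but not in the listed primary and secondary objectives or the overarching research question. That lowers the severity without removing the conflict.

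**Conclusion.** The point holds as an internal contradiction with a practical consequence. Following the conditional sentence would leave a stated aim unanswered after a non-superior result, although the primary economic measure does not depend on PSS-14 and MBCT-L is the longer programme with the greater staffing demand.

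With superior read as two-sided p<0.05 favouring MBCT-L on 20-week PSS-14, and an SE of 1.59 to 1.82, the analysis would not be run in about 12% to 22% of trials at the planned 5 points and in 97.5% at no difference. Selection on significance is a secondary point: a 7% to 14% overstatement of the PSS-14 benefit at 5 points, and undetermined for QALYs.

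This should be corrected, but it is not critical. The primary analysis and safety are untouched, and the economic analysis can still be run.

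**What to change.** In Measures of Cost-Effectiveness, delete the condition on superiority. State that incremental costs, incremental QALYs and their uncertainty will be estimated and reported whatever the PSS-14 result, by the methods already given under Economic Analysis. Bring Multimedia Appendix 3 into line if it repeats the condition. The budget impact analysis may stay conditional, as the Discussion has it.

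The cost is one sentence plus health-economist time. The method is written, and the Results section reports that follow-up collection finished on September 30, 2024. The data will be incomplete (follow-up was about 62% when monitored), which the planned imputation analysis already addresses. Sample size and data collection do not change.
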